### Measurements

After the patient has been informed about the study and if agreement to participate, an informed consent form (ICF) will be signed off before any study specific procedures occur.

During the screening, procedures to assure the patient’s eligibility for the study participation will be performed. Females of childbearing potential will have a serum pregnancy test taken. Demographics, medical history including COVID-19 specific history and review of routine blood tests, secondary infections, viral load, radiology, concomitant medications before inclusion will be recorded. Mean new early warning score (NEWS) for the past 24 hours (three measurements 8, 14, 22±2 hours) will be recorded if available (mean is calculated after data are exported from eCRF at the end of study). Baseline NEWS at inclusion will also be recorded. A physical examination will be performed and a HBO-specific questionary as per local routine will be obtained. Subject will be randomised to either HBO (in addition to best practice) or best practice. Routine chemistry and study-specific blood tests will be collected. A complete list of procedures is listed in table 2.

**Table 2 T2:** COVID-19-HBO: list of procedures

Activity	Visit 1	Visit 2	Visit 3	Visit 4	Visit 5	Visit 6	Visit 7	Visit 8	Visit 9
Day	Day 1	Day 2	Day 3	Day 4	Day 5	Day 6	Day 7	Day 14	Day 30
Screening	x								
Inclusion/exclusion criteria	x								
Pregnancy test if woman of childbearing age	x								
HBO-specific medical history/physical examination	x								
Signed informed consent form	x								
Randomisation	x								
1. Medical history	x								
2. Demography*	x	x	x	x	x	x	x	x	x
3. Concomitant medications	x	x	x	x	x	x	x	x	x
4. NEWS score	x, x, x†	x, x, x	x, x, x	x, x, x	x, x, x	x, x, x	x, x, x	x, x, x	x, x, x
5. Standard/study-specific biochemistry	x	x	x	x	x	x	x	x	x
6. Study-specific CBG/ABG	x, x, x†	x, x, x	x, x, x	x, x, x	x, x, x	x, x, x	x, x, x	x, x, x	x, x, x
7. Plasma (microRNA)	x	x	x	x	x	x	x	x	x
8. CBG/ABG HBO	3x	3x	3x	3x	3x	3x	3x		
9. HBO indicated/planned	x	x	x	x	x	x	x		
10. HBO treatment	x	x	x	x	x	x	x		
11. AE	x	x	x	x	x	x	x	x	x
12. ADR	x	x	x	x	x	x	x	x	x
13. UPTD	x	x	x	x	x	x	x	x	x
14. CPTD	x								x
15. ICU admission		x	x	x	x	x	x	x	x
16. Intubation/mechanical ventilation		x	x	x	x	x	x	x	x
17. ICU mortality		x	x	x	x	x	x	x	x
18. Hospital mortality		x	x	x	x	x	x	x	x
19. Overall mortality		x	x	x	x	x	x	x	x
20. Secondary infections	x	x	x	x	x	x	x	x	x
21. Viral load	x	x	x	x	x	x	x	x	x

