22. Staff safety (negative events)	x	x	x	x	x	x	x	x	x
23. Pulmonary CT (check records)	x	x	x	x	x	x	x	x	x
24. Chest X-ray (check records)	x	x	x	x	x	x	x	x	x
25. Chest ultrasound (if available)	x	x	x	x	x	x	x	x	x
26. Extended immunology (n=20)	x			x			x	x	x

CBG/ABG HBO is collected once daily for the first 7 days and if clinically warranted.

All used acronyms and abbreviations are listed in the original protocol (p.9–10, Supplement).

Visit 1–7 is 8-7:59 and visits 8 and 9 are 7 days 8-7:59.

*Visits 2–9 demography check only involves change in DNR status.

†Depending on time of inclusion 1–3 samples/observations will be collected during visit 1 at the specified time points. Additionally, a baseline ABG (if not available from the patient’s medical records) and a baseline NEWS is collected.

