### Trial endpoints

The primary endpoint is the proportion of subjects admitted to ICU from day 1 to day 30 based on predefined criteria for ICU admission. Main secondary efficacy endpoints are 30-day mortality, time to intubation, time to ICU admission and mean change in inflammatory response and main safety endpoints are measurement of adverse event (AE) and serious adverse events (SAE). A list of main efficacy and safety endpoints is listed in table 3.

**Table 3 T3:** COVID-19-HBO: trial endpoints

Primary endpoint	The proportion of subjects admitted to ICU from day 1 to day 30, based on at least one of the following criteria: (1) Rapid progression over hours (2) Lack of improvement on high flow oxygen >40 L/min or non-invasive ventilation with fraction of inspired oxygen (FiO_2_) >0.6 (3) Evolving hypercapnia or increased work of breathing not responding to increased oxygen despite maximum standard of care available outside ICU (4) Haemodynamic instability or multiorgan failure with maximum standard of care available outside ICU
Secondary endpoints	(in selection)
Main secondary efficacy endpoints	(1) Proportion of subjects with 30-day mortality, all-cause mortality, from day 1 to day 30.
	(2) Time-to-intubation, that is, cumulative days free of invasive mechanical ventilation, from day 1 to day 30
	(3) Time-to-ICU, that is, cumulative ICU free days, derived as the number of days from day 1 to ICU, where all ICU free subjects are censored at day 30
	(4) Mean change in inflammatory response from day 1 to day 30 White cell count+differentiation Procalcitonin C-reactive protein Cytokines (IL-6) (if available at local laboratory) Ferritin D-dimer LDH
	(5) Overall survival
Safety endpoints	(1) The number of subjects, proportion of subjects and number of events of AE
	(2) The number of subjects, proportion of subjects and number of events of SAE
	(3) The number of subjects, proportion of subjects and number of events of SADR
	(4) Mean change in PaO_2_/FiO_2_ before and after HBO compared with mean variance in PaO_2_/FiO_2_ in the control group during day 1 to day 7
	(5) Mean change in NEWS before and after HBO compared with mean change in daily NEWS in the control group during day 1 day 7
	(6) Number of negative events in staff associated with treatment of subject (eg, contact with aerosol from subject), number of events from day 1 to day 30 or last day in hospital if subject is discharged earlier, or at withdrawal

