### Statistical analysis

*Power calculation*: the primary endpoint ICU admission is defined by criteria for selection for ICU. We have assumed that 50% of the subjects will have at least one criterion during the course of the study and we aim to reduce the ICU admission rate by 40%, that is, to an ICU admission rate of 30%. To achieve 80% power with type-I error rate of 0.05 (two-tailed), a sample size of 93 subjects per group is required. We plan to enrol 200 subjects into this trial. Interim analyses may decide to recalculate sample-size for the trial.

Sample size calculation was done in nQuery V.7.

Primary and secondary endpoints will be evaluated using the intent-to-treat population (ie, all randomised subjects) and the primary endpoint also using the per protocol population (ie, all randomised subjects with no major protocol violations). All randomised subjects will be included in the safety population. The primary analysis of the primary endpoint will be performed using the Cochran Mantel Haenszel test adjusting for randomisation strata site and gender.

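### Table 3 censors every ICU-free subject at day 30, with no exception for death or withdrawal, and labels two time-to-event endpoints as counts of free days

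*Protocol article*

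**What the plan says.** The relevant text is in the protocol article, section Trial endpoints, Table 3, main secondary efficacy endpoints.

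- Endpoint (3) begins "Time-to-ICU, that is, cumulative ICU free days" and is then "derived as the number of days from day 1 to ICU, where all ICU free subjects are censored at day 30". No exception is printed for death, withdrawal or loss to follow-up.
- Endpoint (2) reads "Time-to-intubation, that is, cumulative days free of invasive mechanical ventilation, from day 1 to day 30". No derivation and no censoring rule follow.
- Death is counted on its own in endpoint (1), "Proportion of subjects with 30-day mortality, all-cause mortality, from day 1 to day 30", and in endpoint (5), overall survival.
- Safety endpoint (6) in the same table does let observation end early: "number of events from day 1 to day 30 or last day in hospital if subject is discharged earlier, or at withdrawal".

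The section Statistical analysis adds: "Primary and secondary endpoints will be evaluated using the intent-to-treat population (ie, all randomised subjects". Withdrawn and deceased subjects therefore stay in these analyses and need a value. The section Hypothesis and objectives lists ICU resource load, morbidity and mortality among the main secondary objectives.

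**The concern.** There are two separate problems.

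**Censoring.** The derivation applies to every ICU-free subject. A censoring time of day 30 states that the subject was observed without ICU admission up to day 30. That is untrue for someone who left the study earlier. For someone who died on the ward it is true only in the sense that no admission could follow, and reporting the result as ICU-free days makes it look like a good outcome.

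**Labels.** Time to a first event and a cumulative count of event-free days are different quantities and need different analyses. Endpoint (2) offers both in one line and does not choose. Endpoint (3) chooses time to first admission through its derivation but keeps the free-days label, so a one-day and a three-week ICU stay starting on the same day score alike. That matters for an endpoint that would be read as evidence on ICU load.

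At stake is whether a difference on endpoints (2) and (3) can be read as benefit. In an open-label trial, leaving the choice of quantity open also leaves room to choose it after outcomes are known.

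**Working it through.** **1. The plan's own figure.** Endpoints (2) and (3) have no stated figure. For the primary endpoint (50% vs 30%, two-sided 0.05, 80% power):

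n = [1.960·√(2·0.4·0.6) + 0.842·√(0.5·0.5 + 0.3·0.7)]² / 0.2² = (1.358 + 0.571)² / 0.04 ≈ 93 per group.

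This reproduces the article's 93. It does not depend on endpoints (2) or (3).

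**2. The day-30 rule applied to single subjects** (scoring day 30 as 30):

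| Subject | Value under the printed rule |
|---|---|
| Alive and ICU-free at day 30 | 30, censored |
| Dies on the ward on day 5, never in ICU | 30, censored |
| Withdraws on day 5, never in ICU | 30, censored; 30 − 5 = 25 days unobserved |

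**3. Label against gloss in endpoint (2).** Take a subject intubated on day 5, extubated on day 10 and alive at day 30. Time to first intubation is 5 − 1 = 4 days (5 if day 1 is counted). Ventilated time is 10 − 5 = 5 days, so ventilation-free days are 30 − 5 = 25. The two measures disagree for anyone extubated before day 30.

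**4. Can death without ICU occur?** Table 2 lists "18. Hospital mortality" separately from ICU mortality, and its footnote says "Visits 2–9 demography check only involves change in DNR status", so changes in resuscitation status are expected. The Wuhan cohort cited in the Introduction had 28% hospital mortality, 26% ICU admission and 19% mechanical ventilation or extracorporeal support. At least 28 − 26 = 2 percentage points died without ICU, and at least 28 − 19 = 9 without such support. That is another population, so it shows only that the case is real.

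**5. How much can the handling of death matter?** Simulation with 100 per arm, 1,000 runs, event days uniform over days 2 to 14 and a log-rank test at |z| > 1.96. The 50% and 30% ICU rates are the article's planning figures; all other rates and the timing are assumptions. Entries are the percentage of runs rejecting.

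| ICU / ward death: control; HBO | Censored at day 30 | Censored at death | ICU or death |
|---|---|---|---|
| 50/5; 50/5 | 5.5 | 5.5 | 5.9 |
| 50/5; 30/5 | 82.3 | 82.8 | 81.2 |
| 50/5; 45/10 | 10.4 | 7.9 | 4.4 |
| 50/0; 40/10 | 30.3 | 20.2 | 6.1 |
| 50/0; 30/20 | 82.6 | 65.2 | 6.1 |

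With balanced ward deaths (first two rows) the rules agree. In the last three rows ICU-or-death is equal in the two arms (55%, 50% and 50%), and the rules diverge as the imbalance in ward deaths grows. In the last row, if the values are averaged as free days, the event days have mean 8, so control gets 0.5·8 + 0.5·30 = 19.0 and HBO 0.3·8 + 0.7·30 = 23.4. The simulated means are 18.9 and 23.5. The apparent gain is about 4.5 days although equally many subjects reach ICU or die.

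Rejections in the last three rows are not false positives for ICU incidence, which does differ there. They mislead only if read as subjects faring better. Withdrawals were not simulated.

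**The case against.** Three arguments on the other side carry weight.

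*The article is a summary.* It refers to a full protocol as a supplement and prints its secondary endpoints as a selection. Handling of death and loss is often left to the full protocol or the analysis plan, and the day-30 phrase may be meant as the ordinary administrative cut-off. Silence would indeed be no fault. But the table prints a derivation that covers all ICU-free subjects, and it is that wording that is criticised. The full protocol may qualify it.

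*For deaths, the rule can be defended.* Keeping subjects who die without ICU in the risk set to day 30 corresponds to a cumulative-incidence (subdistribution) analysis with death as a competing event. It answers how many were admitted and when, which fits the primary endpoint, and mortality is reported separately in the same table. This stands: a composite is a different question, not the only right one. The defence needs the approach to be named. It does not rescue the free-days label, and it does not extend to withdrawals.

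*Endpoint (2) has no censoring rule.* A reader might infer that a subject who dies unintubated also receives the maximum score, so that two endpoints reward early death. The text does not support that: the day-30 rule is printed for endpoint (3) only. Endpoint (2) is ambiguous about which quantity is meant, and no more can be said of it. Likewise, the derivation in endpoint (3) settles that it is time to first admission; only its label is wrong.

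**Conclusion.** The point holds as a correction to two secondary endpoints. As printed, the time-to-ICU rule treats unobserved time after withdrawal as ICU-free and makes ward deaths indistinguishable from ICU-free survivors. Endpoint (2) names two quantities that can differ widely (4 to 5 against 25 days in the example), and endpoint (3) carries a label that ignores ICU length of stay.

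The size cannot be fixed from the article, because it gives no ward-death or withdrawal rates by arm. With equal 5% ward deaths the three rules reject in 81% to 83% of runs when ICU rates are 50% and 30%, so the choice hardly matters. With an assumed 0% against 20% it decides the result: 83% under the printed rule, 6% for ICU-or-death.

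A reader might go further and conclude that these endpoints cannot support any statement on ICU load or morbidity, or that the trial's main result is in doubt. The documents do not support either. The effect is small if ward deaths and withdrawals are rare or balanced, and the primary endpoint definition and its sample size are unaffected.

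**What to change.** 1. Define time to first ICU admission and time to first intubation, each to day 30. Censor withdrawn or lost subjects at last known status.
2. State how death without the event is handled: either as a competing event, with cumulative incidence reported beside mortality, or as part of an ICU-or-death and an intubation-or-death composite.
3. If free days are wanted for ICU load, define them as separate endpoints under their own names: days alive and outside ICU, and days alive and off the ventilator, to day 30, with subjects who die scored 0. Remove the free-days wording from the time-to-event endpoints.

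The cost is endpoint wording and programming. Table 2 already records ICU admission, intubation or ventilation, and mortality at visits 2 to 9. Item 3 also needs ICU discharge and extubation dates. The article does not show whether the case report form holds them, but every visit includes a review of the medical records since the last one. With 31 of 200 subjects randomised at the time of writing, the change can still be made early in the trial.

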### Interventions

HBO in addition to best practice compared with best practice

HBO: HBO 1.6–2.4 Atmospheres Absolute for 30–60 min, maximum five treatments first 7 days

Control: best practice treatment for COVID-19

The first HBO treatment will be given within 24 hours after inclusion. Patients with respiratory symptoms admitted to the hospital will be informed and asked to participate. The patients will be included once they fulfil the inclusion criteria and none of the exclusion criteria, but the timing of the HBO treatment will depend on available resources.

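### Safety endpoints 4 and 5 define a different quantity in each arm, so their between-arm contrasts do not isolate an HBO effect

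*Protocol article*

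**What the plan says.** Table 3 (Trial endpoints) gives the two definitions. Endpoint 4 is a mean change in PaO2/FiO2 "before and after HBO compared with mean variance in" that ratio among controls over days 1 to 7. Endpoint 5 is "Mean change in NEWS before and after HBO compared with mean change in daily NEWS in the control group during day 1 day 7".

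Other parts of the article bear on them:

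- Interventions: HBO is given "for 30–60 min, maximum five treatments first 7 days", and "the timing of the HBO treatment will depend on available resources".
- Table 2: NEWS (row 4) and "6. Study-specific CBG/ABG" are each listed three times per visit on visits 1 to 9, with no restriction by arm. Row 8 lists HBO-linked blood gases on visits 1 to 7. No row lists a session-linked NEWS. No time before or after a session is given for any reading.
- Measurements: the clock times "three measurements 8, 14, 22±2 hours" are stated for NEWS in the 24 hours before inclusion.
- Statistical analysis: every randomised subject belongs to the safety population. A test is named only for the primary endpoint.
- Trial endpoints: AE and SAE are named as the main safety endpoints.

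**The concern.** A between-arm comparison measures a treatment effect only if the same quantity, over the same interval, is taken in both arms and on the subjects as randomised. Endpoints 4 and 5 depart from this in three ways.

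1. **Kind of quantity (endpoint 4).** A signed change in mm Hg is set against a variance, which is in mm Hg squared and cannot be negative. Equality of the two is not the hypothesis of no effect.
2. **Interval (endpoint 5, and endpoint 4 if variance is loose wording for change).** The HBO figure spans the time around a session. The control figure spans a day, or the whole of days 1 to 7.
3. **Subjects and days.** Only subjects who receive HBO, on at most five occasions, have a session-linked change. All controls contribute over seven days. A subject randomised to HBO but never treated has no value, although that subject is in the safety population. The contrast is thus conditioned on something that happens after randomisation.

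The article names oxygen toxicity in inflamed lungs as a concern (Remaining gap of evidence). Under a worsening trend the interval mismatch makes HBO look better than it is; under an improving trend it makes HBO look worse.

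**Working it through.** **Figures in the plan.** The article gives none for endpoints 4 and 5. Its sample size rests on the primary endpoint and reproduces: with 50% against 30%, two-sided 0.05 and 80% power, n = [1.960·√(2·0.4·0.6) + 0.842·√(0.5·0.5 + 0.3·0.7)]² / 0.2² = (1.358 + 0.571)² / 0.04 ≈ 93 per group, as stated. Nothing below changes it.

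**Assumptions (not in the article).** HBO has no effect. Within-patient SD σ is 10 to 30 mm Hg for PaO2/FiO2 and 1 to 1.5 points for NEWS. The linear trend d is 0 or ±5 mm Hg per day for PaO2/FiO2, and −0.5 to +1 point per day for NEWS. The readings before and after a session are h hours apart.

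**Expected values with no HBO effect.**

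- Change around a session: d·h/24.
- Control variance over days 1 to 7: σ² + 4.26·d², where 4.26 is the variance in days² of 21 reading times (8, 14 and 22 h on seven days).
- Control daily change: d. Control change from day 1 to day 7: 6d.
- Interval bias, HBO minus control daily change: d·(h/24 − 1). It is zero when d = 0.

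**Endpoint 4, variance read literally.** With d = 0 the HBO change is 0 and the control figure is 10² = 100 to 30² = 900 mm Hg squared. With d = ±5 and h = 6 the HBO change is ±5·6/24 = ±1.25, against 100 + 4.26·25 = 206.5 up to 900 + 106.5 = 1,006.5.

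**Endpoint 4, variance read as change.** With d = ±5 and h = 6 it is ±1.25 against ±5 (daily) or ±30 (day 1 to day 7).

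**Endpoint 5.** With d = 0.5 the control daily change is 0.50. The HBO change is 0.5·1/24 = 0.02 if h = 1, 0.125 if h = 6, and 0.17 if h = 8. The bias is −0.48, −0.375 and −0.33.

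**Simulation as a check.** There were 100 subjects per arm, three readings a day for seven days, five sessions, h = 6, no HBO effect and 2,000 runs. A Welch test at 0.05 served only as a yardstick, since the article names no test for these endpoints.

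| Control quantity | Trend per day | HBO mean | Control mean | Null rejections |
|---|---|---|---|---|
| PaO2/FiO2 variance | 0 | 0 | 100 to 900 | 100% |
| PaO2/FiO2 variance | ±5 | about ±1.25 | 206 to 1,007 | 100% |
| PaO2/FiO2 SD | 0 or ±5 | 0 or about ±1.25 | 9.9 to 31.3 | 100% |
| PaO2/FiO2 daily change | 0 | 0 | 0 | about 5% |
| PaO2/FiO2 daily change | ±5 | about ±1.25 | ±5.0 | 47–100% |
| NEWS daily change | 0 | 0 | 0 | about 5% |
| NEWS daily change | 0.25 | 0.07 | 0.25 | 47–80% |
| NEWS daily change | ±0.5 | ±0.12 to 0.13 | ±0.50 | 97–100% |
| NEWS daily change | 1 | 0.25 | 1.00 | 100% |
| Same clock window and days in both arms | all of the above | – | – | 4–6% |

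**Conditioning on treatment.** The article gives no expected share of HBO subjects left untreated or of planned sessions missed, so no size is put on this part.

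**The case against.** The strongest reply is that *variance* is loose wording. Endpoint 5, on the next line and built the same way, uses change for the controls, so the authors may have meant change in endpoint 4 too. That is plausible, and it removes the mismatch of units. It leaves the mismatch of interval and of subjects, and the text does not say which meaning applies.

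A second reply is that this is a condensed article, whose full protocol may define reading windows and derivations. That is fair for missing detail, and no detail is criticised here as missing. The fault is in the definitions that the article does state.

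A reader might infer more than the documents support:

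- *That endpoint 5 is invalid in every case.* Both arms are on one scale, and with no time trend the interval mismatch causes no bias. A trend is likely in patients selected as likely to need ICU, but its size is assumed here.
- *That the HBO change covers 30 to 60 minutes.* That is the length of a session. The times of the surrounding readings are not given, so h is unknown.
- *That the trial could neither show nor exclude respiratory harm.* AE, SAE and SADR are separate endpoints, ICU admission and time to intubation are compared between arms, and an independent DSMB reviews safety.
- *That a false-positive test is planned.* No test is stated for these endpoints, and the comparison may be descriptive. The rejection rates only show how far apart the two quantities lie.

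**Conclusion.** The point holds for both endpoints as defined. Endpoint 4, read literally or as an SD, sets a figure near zero against one that is always positive, whatever HBO does; this direction does not depend on the assumed SD. Endpoint 5, and endpoint 4 if change was meant, is biased by d·(h/24 − 1) whenever values trend. At the assumed 0.5 NEWS point per day and 6 h between readings, that is −0.375 point with no HBO effect; with no trend it is zero. Separately, the contrast leaves out untreated HBO subjects, which conflicts with a safety population of all randomised subjects.

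This should be corrected before analysis. It is not critical to the trial: these are supporting safety endpoints, and the primary endpoint, the 93 per group and the main safety endpoints stand.

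**What to change.** - Remove the variance wording from endpoint 4 and define one identical measure for both arms in all randomised subjects. An example is the change from baseline in scheduled PaO2/FiO2 and NEWS over days 1 to 7, adjusted for baseline and taken on the same days in both arms, using the readings in Table 2 rows 4 and 6. The exact model can be left to the SAP.
- Report changes before and after sessions descriptively, within the HBO arm only, and state when those readings are taken. Row 8 of Table 2 shows three HBO blood gases per visit while its footnote says once daily; the two should be reconciled.

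The cost is rewording two endpoints and some programming. There are two limits. Row 6 allows capillary as well as arterial samples, so PaO2/FiO2 may be incomplete where no arterial sample was taken. The 8, 14 and 22 h times are spelled out only for NEWS before inclusion, so the times of the later readings should be confirmed before they are used as a common schedule.
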